### 7.2.6 Medication Exclusions

In addition to these medical and psychiatric inclusion/exclusion criteria, participants will be required to abstain from medications/supplements that might interact with, or impact the experience of, psilocybin administration. This strategy is proposed both to enhance safety (i.e. by limiting co-exposure to medications that might increase potential serotonin-related side effects of psilocybin) and to reduce biological heterogeneity of participants entering the intervention session.

Patients with ongoing antidepressant treatment are excluded to avoid difficulties in interpretation of results from psilocybin treatment. This exclusion is also expected to result in a cohort more representative of the future target patient group, assuming approval of psilocybin as a depression treatment. The time that patients should be off treatment is at least 30 days prior to screening.

### 7.2.7 Blood Pressure

The Screening and Baseline blood pressure criteria are in place for both safety and feasibility reasons. First, the American College of Cardiology and American Heart Association recently lowered their criteria for Stage 1 hypertension from SBP 140 mmHg/DBP 90 mmHg to SBP 130 mmHg/DBP 80 mmHg, citing strong observational data to support this change. By lowering the Screening BP criteria to SBP > 135 mmHg or DBP > 85 mmHg, the study will in effect recruit a healthier population that is at less risk for cardiovascular events. Second, due to the nature of the study, it is likely that some percentage of participants will present on the dosing day with vital signs elevated above Baseline values due to anxiety over the upcoming procedure (i.e. "white coat syndrome"). By reducing the Screening criteria to 135/85 mmHg, it is expected that the number of participants who fail to meet the dosing day (pre-dose) BP criteria of <140/90 mmHg due to elevated BP resulting from anxiety will be reduced. This change will significantly reduce the time burden and psychological stress on participants who would otherwise qualify but fail to meet BP criteria on the dosing day. Importantly, by setting more stringent BP parameters at screening we will also reduce the number of participants who will unnecessarily taper off from psychotropic agents and psychotherapy prior to dosing day should they be discontinued due to "white coat syndrome" elevation of BP on dosing day.

## 8. SCREENING PROCESS AND PROCEDURES

Study screening procedures and their timing are summarized in the Schedule of Assessments (Table 1). Participants will be provided with visit reminders. Adherence to the study design requirements, including those specified in the Schedule of Assessments, is essential and required for study conduct.

### 8.1 Recruitment

Participants for the study will/may be recruited from the following sources: 1) a study specific website, 2) relevant clinical programs at Norra Stockholms Psykiatri, SLSO; 3) via advertisements on the web, and 4) via relevant national clinician-focused listservs and patient-advocate listservs. All advertisements will be approved by the IRB prior to posting. As this study will require intensive study recruitment measures and new and various

recruitment opportunities are found often, there may be instances of recruitment which do not fall under the above categories. However, prior to initiation of any recruitment activities, approval will be obtained from the IRB.

## 8.2 Study Recruitment Website and Pre-Screener Questionnaire

A clinical research recruitment website will serve as the anchor for the patient recruitment efforts and as the hub for study digital recruitment activities. The website contains basic educational content about the clinical trial, depression and psilocybin. The study profile page provides key study details for prospective participants. Study profile page visitors who are interested in participating in the study may complete an eligibility pre-screener questionnaire.

### Pre-Screener Questionnaire

The pre-screener includes questions regarding demographics and availability, medical and mental health questions, and prior psychedelic and other drug use including alcohol. It also includes a waiver of documentation of consent as it does not present more than minimal risk of harm to participants and involves no procedures for which written consent is normally required outside of the research context. During the pre-screener, participants will be informed, via the website, that answering questions is voluntary and that any information shared will be kept confidential. Identifiable contact information will be encrypted.

## 8.3 Telephone Screen

Prospective participants will be prescreened by telephone to learn if they meet basic eligibility criteria. The Telephone Screen will include questions similar to the pre-screener regarding demographics and availability, medical and mental health questions, and prior psychedelic and other illicit drug use.

If at any time during the telephone screen process a potential participant discloses suicidal ideation, he or she will be immediately encouraged to call 112.

If the initial telephone screen suggests that the participant is eligible, an In-Person Screening visit will be scheduled. If the participant does not qualify or decides not to participate the reason will be documented in the Electronic Data Capture (EDC) system with all identifiable information encrypted.

Telephone Screen information will be verified at the In-Person Screening visit prior to written informed consent.

## 8.4 Written Informed Consent

For this trial, written informed consent will occur at the initial In-Person Screening visit. Study participants will be considered enrolled in the study when they provide written informed consent. All individuals who sign an ICF will be assigned a participant ID number in the EDC, which will be assigned sequentially. Written informed consent will be obtained in person from all participants before undergoing any study procedures. Prisoners, pregnant women and mentally impaired persons will not be included. Competent persons meeting other eligibility criteria will be welcomed, regardless of race, gender, ethnicity, religion or

socioeconomic status. Additionally, students, employees, patients or family members affiliated with the PI(s) will not be enrolled, and family members of any study team member will be prohibited from participating in this study.

The following consent process will be adhered to for each participant:

- The PI or a qualified representative will explain the screening process and nature of the study to the participant and answer all questions.
- Participants must be informed that their participation is voluntary and that he/she may withdraw from the study at any time, for any reason.
- Participants will be provided adequate time for review and discussion prior to his/her making a decision about participation in the study, including the option to take the information home to discuss with family prior to making a decision.
- Participants will be required to sign a statement of informed consent that meets the current requirements of ICH guidelines, and the Institutional Review Board (IRB).
- Participants will be encouraged to ask any questions at any time for any reason, and to seek outside counsel when appropriate.
- To verify informed consent was obtained before the participant was enrolled in the study, the ICFs will contain the date and time written consent was obtained. The authorized person obtaining informed consent must also sign the ICFs.
- Participants must be re-consented to the most current version of the ICFs during their participation in the study, per institutional IRB requirements, and they will be informed of any changes to the consent form.
- A copy of the ICFs must be provided to the participant.

The ICF and any other written participant information to be provided to participants will be revised whenever important new information becomes available that may be relevant to the participant's consent. Any revised ICF and written participant information will receive IRB approval before being implemented. The participant will be informed of any changes and re-consented with the current version of the consent form and provided a copy at their next visit. Communication of this information to the participant will be documented.

## **8.5 In-Person Screening Visit (7-35 days prior to dose)**

After preliminary eligibility is determined via the Telephone Screen, an in-clinic screening will occur at Norra Stockholms Psykiatri. The purpose of the In-Person Screening visit is to confirm eligibility for the study. Upon signing the Informed Consent Form (ICF), the potential participant may commence study-related screening activities. No study related procedures, other than the study pre-screening questionnaire and telephone screen, will occur prior to obtaining written informed consent.

Screening will take 7 to 35 days to allow for full medical and psychiatric evaluation. The purpose of the Screening visit is to evaluate medical and psychiatric appropriateness for the study. If at any point the participant is found to be ineligible, the screening process may be discontinued, and any remaining procedures will not take place.

### **8.5.1 Inclusion/ Exclusion Criteria Confirmation**

Following the completion of all Screening medical and psychiatric assessments, the PI will confirm participant eligibility on an ongoing basis until dosing.

### **8.5.2 Magnetic Resonance Imaging (MRI)**

After informed consent and before Lumbar Puncture (day 7-35 before dosing), MRI1 will take place at MR-centrum Solna. The visit will take approximately 1 hour and will include structural functional sequences including a set of tasks (see 14).

### **8.5.3 Lumbar puncture**

The first lumbar puncture (LP; day 7-35 before dosing) for acquisition of Cerebro Spinal Fluid (CSF) will be performed at a separate visit. This is done after written or verbal report of the MRI examination within the screening process has confirmed absence of signs of increased intracerebral pressure. The LP will take place at Norra Stockolms Psykiatri, Mottagningen för hjärnstimulering or the PET center, or another medical site and will be performed by a registered physician according to standard procedures in local anaesthesia. All together at least 5 ml CSF will be sampled.

### **8.5.4 PET1**

The first [C]UCB-J PET examination will take place after LP and before dosing (1-7 days). The examination will be performed at the PET-center at Karolinska Solna and the visit including preparations will take approximately 3 hours. At the visit a rater based MADRS and blood sampling will be performed. Urine samples for toxicology and, if applicable, pregnancy, will be analysed prior to the PET examination.

## **9. PREPARATION, RANDOMIZATION, DOSING AND FOLLOW UP PROCEDURES**

This section outlines the purpose and content of all preparation, randomization, dosing and follow up study procedures. Participants will be provided with visit reminders. For the timing and frequency of assessments at each visit see Table 1.

### **9.1 Preparatory Sessions with Clinical Facilitators (1 day prior to dose)**

Following successful completion of Screening, participants will be assigned a Lead Clinical Facilitator and a Co-Facilitator. Both Facilitators will remain with the participant throughout the preparatory, dosing, and integration sessions.

The main objective during preparatory session is to build rapport and therapeutic alliance between the participant and Session Facilitators, as support for the participant as they navigate the dosing session. Participants will meet with both the Facilitators, who will also attend the participant's dosing session. Whenever possible, these meetings will occur in the room in which dosing will take place, so participants can develop a level of comfort and familiarity with the intervention location. Consistent with previous psilocybin protocols, the participant's life history and current situation in life will be reviewed, and intentions and expectations for the intervention session will be discussed.

### 9.1.1 Post Preparatory Session Assessment (1 day prior to dose)

This assessment can occur on the same day as the preparatory assessment but must be performed after all preparatory session activities are complete. Before dosing, Facilitators will communicate with the PI or and Study Physician to discuss overall appropriateness for dosing. If the Facilitators, PI or Study Physician believes the dosing session is contraindicated, the session will be cancelled or postponed (Table 1; confirm eligibility#2).

## 9.2 Randomization

Randomization will occur for participants who have been determined to be eligible for the study and will occur the morning prior to dosing. Following this, participants will be randomized to one of two intervention groups. Participants are randomized in blocks in a 1:1 ratio in a blinded fashion to the psilocybin group or the active control group. The block size will not be shared. Randomization will be done at the site by strictly following a randomization list in sequential order. If a patient is replaced the new patient will be allocated a randomization number with the same treatment while keeping the double blinded allocation. This will be performed by having back-up blinded treatment allocations for each subject in sealed envelopes. These will only be used and opened following withdrawal. Importantly, the allocated treatment will remain blinded for both the withdrawn and replacement subject as well as for the study team.

The master randomization code will be maintained in a secured location until the time of unblinding. Individual emergency envelopes will be available at the site in case the investigator for safety reasons has to break the blind for a specific patient.

## 9.3 Day 0: Dosing Session

Participants will be asked to report to the research site, Mottagningen för Hjärnstimulering, NSP, ST Görans sjukhusområde, in the morning. Sessions are expected to last 6-10 hours.

### 9.3.1 Pre-Dose

Upon arrival, and prior to the dosing, the following assessments will occur:

1. Study personnel will inquire about any possible changes in health
2. Study personnel will inquire about any change in concomitant medication use and adherence.
3. A urine drug test for drugs of abuse will be performed
4. Urine pregnancy testing (women of childbearing potential only) will be performed
5. The study coordinator will remind the participant of their agreement to the following during the dosing session, as previously agreed to during the preparation sessions (also see Manual for Clinical Facilitators for agreements):
  - o The participant agrees to remain on-site for a minimum of 7 hours on their dosing day after ingesting the psilocybin or placebo capsule and all identified study personnel agree that the participant may safely leave the facility with their identified support person.

- o The participant agrees to call the site and/or 112 if he or she has suicidal thoughts or feelings throughout the duration of the study.
6. Pre-Dose vital signs (Blood Pressure and Heart Rate)

#### Urine Drug Test Results

A negative urine drug test will be required the morning of dosing prior to drug administration. The Study Physician will be notified of urine drug test results. A positive urine drug test will result in the dose being canceled with no option for future rescheduling. The patient will be withdrawn from the study.

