  - a. Screening blood pressure SBP >135 mmHg or DBP > 85 mmHg on three separate readings; or
  - b. Baseline blood pressure SBP >140 mmHg or DBP > 90 mmHg on three separate readings
11. Have a history of stroke or Transient Ischemic Attack (TIA)
12. Have moderate to severe hepatic impairment, as indexed by a Child-Pugh score  $\geq 7$
13. Have epilepsy
14. Have insulin-dependent diabetes
15. Are unable or unwilling to adhere to the following medication requirements:
  - a. Agree to suspend sildenafil (Viagra®), tadalafil, or similar medications at least 72 hours prior to dosing
  - b. If taking any supplement containing >20 mg of niacin, agrees to suspend use for the duration of the study
16. Have a positive urine drug test including Amphetamines, Barbiturates, Buprenorphine, Benzodiazepines, Cocaine, Cannabis, Methamphetamine, MDMA, Methadone, Opiates (Morphine, Oxycodone), Phencyclidine (PCP), and Tetrahydrocannabinol (THC). Exceptions are made for prescribed Benzodiazepines (stable dose for sleep or anxiety). *Note:* Benzodiazepine medications for sleep and non-benzodiazepine sleeping medications will be allowed to at discretion of the research physician. *Note:* Participants using cannabis, including legal cannabis, for any purposes will be excluded. *Note:* Participants who are taking prescription maintenance opiates, methadone or buprenorphine naloxone will be excluded.
17. Nicotine dependence that would disallow an individual to be nicotine free for the 7-10 hours during the dosing period

18. Meet ICD-10 criteria for schizophrenia spectrum or other psychotic disorders, including MDD with psychotic features (except substance/medication-induced or due to another medical condition), or Bipolar I, Bipolar II Disorder and Bipolar Disorder Not Otherwise Specified. *Note:* Participants with any lifetime diagnosis of schizophrenia spectrum or other psychotic disorders will be excluded
19. Meet ICD-10 criteria for antisocial personality disorder
20. Meet ICD-10 criteria for a moderate or severe alcohol or drug use disorder (excluding caffeine). *Note:* Participants with a diagnosis of alcohol or drug use disorder within the past 12 months will be excluded
21. Have presence of any psychiatric condition or symptom judged by the PI (or designee) to be a more significant clinical problem than MDD for the participant.

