  - b. Baseline blood pressure SBP >140 mmHg or DBP > 90 mmHg on three separate readings
10. Have a history of stroke or Transient Ischemic Attack (TIA)
11. Have moderate to severe hepatic impairment, as indexed by a Child-Pugh score  $\geq 7$
12. Have epilepsy
13. Have insulin-dependent diabetes
  - o Note: Participants who are taking oral hypoglycemic agent and have a history of hypoglycemia requiring medical intervention will be excluded
14. Are unable or unwilling to adhere to the following medication requirements:
  - a. Agree to suspend sildenafil (Viagra®), tadalafil, or similar medications at least 72 hours prior to dosing
  - b. If taking any supplement containing >20 mg of niacin, agrees to suspend use for the duration of the study
15. Have a positive urine drug test including Amphetamines, Barbiturates, Buprenorphine, Benzodiazepines, Cocaine, Cannabis, Methamphetamine, MDMA, Methadone, Opiates (Morphine, Oxycodone), Phencyclidine (PCP), and Tetrahydrocannabinol (THC). Exceptions are made for prescribed Benzodiazepines (stable dose for sleep or anxiety).
  - o Note: Benzodiazepine medications for sleep and non-benzodiazepine sleeping medications will be allowed to continue through the study period for participants who have been on a stable dose of such a medicine for at least 6 weeks prior to Screening, as determined during review of concomitant medications
  - o Note: Participants using cannabis, including legal cannabis, for any purposes will be excluded
  - o Note: Participants who are taking prescription maintenance methadone or buprenorphine naloxone will be excluded
  - o Note: Prescription opiates must have been stopped at least 5x the elimination half-life of the specific drug at the time of inclusion, as confirmed with a negative urine drug screen.
16. Nicotine dependence that would disallow an individual to be nicotine free for the 7-10 hours during the dosing period
17. Meet ICD-10 criteria for schizophrenia spectrum or other psychotic disorders, including MDD with psychotic features (except substance/medication-induced or due to another medical condition), or Bipolar I Disorder, Bipolar II Disorder and bipolar disorder NOS.
  - o Note: Participants with any lifetime diagnosis of schizophrenia spectrum or other psychotic disorders will be excluded
18. Meet ICD-10 criteria for antisocial personality disorder
19. Meet ICD-10 criteria for a moderate or severe alcohol or drug use disorder (excluding caffeine)

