### 7.2.2 Benzodiazepines

Benzodiazepine medications for sleep and non-benzodiazepine sleeping medications will be allowed for participants who have been on a stable dose of such a medicine for at least 6 weeks prior to Screening. These medications are allowed because they have no psychotropic effects that might confound any potential differential antidepressant signal from the

psilocybin vs. niacin placebo. On the other hand, requiring discontinuation of these sleeping agents prior to study drug dosing would likely disrupt stable sleep patterns that were part of the pre-treatment depressive symptom profile, and by doing this might interfere with potential antidepressant signals from the study drugs. Because these agents are used at bedtime, they will be out of participants' systems prior to study drug dosing and thus should not interfere with either psychodynamic or pharmacokinetic properties of psilocybin.

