|                                                                                                                                                                                                             |            | If repeat BP is < 140 mmHg and < 90 mmHg, proceed with dosing                                                                                  |
|                                                                                                                                                                                                             |            | If three readings are elevated  , consult with the study physician for further evaluation and follow up.                           |

The initial reading should occur after the participant has been recumbent a minimum of 10 minutes

Dosing may be rescheduled at the discretion of the site PI or study physician. If > 7 days have elapsed since the Baseline visit, all Baseline measures must be repeated before dosing. If > 40 days have elapsed since the original Screening date the participant will be unable to participate in the study.

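### Section 9.3.1 withdraws any patient with a positive dosing-morning urine drug test, with no exemption for the stable-dose benzodiazepines that exclusion 15 permits

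*Protocol*

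**What the plan says.** **Eligibility.** Exclusion 15 in Protocol 7.1.2 excludes patients with a positive urine drug test and names benzodiazepines among the substances tested. It then adds: "Exceptions are made for prescribed Benzodiazepines (stable dose for sleep or anxiety"). A note says that benzodiazepines for sleep and other sleeping medicines "will be allowed to continue through the study period for participants who have been on a stable dose" for at least six weeks before Screening. Synopsis no. 16 has the same exception, but its note says only that sleep medicines "will be allowed to at discretion of the research physician".

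**Rationale.** Section 7.2.2 explains why stable sleep medication is kept: stopping it could disturb sleep and obscure an antidepressant signal. It expects no interference on the day: "Because these agents are used at bedtime, they will be out of" the patient's system before dosing.

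**Dosing morning.** Section 9.3.1, item 3: "A urine drug test for drugs of abuse will be performed". The paragraph on results requires a negative test, has the Study Physician notified, and continues: "A positive urine drug test will result in the dose being canceled with no option for future rescheduling". The patient is then withdrawn.

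**Schedules.** Section 5.6.3 places urine drug and pregnancy tests at screening, PET1 and PET2. The Table 1 row for urine toxicology and pregnancy has no Day 0 entry.

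**The concern.** An exemption from a positive-urine criterion makes sense only if some enrolled patients are expected to test positive from a permitted drug. Section 9.3.1 gives that same finding the opposite consequence on Day 0, after the invasive baseline work is done.

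Staff facing such a result have two options, both poor. They can follow 9.3.1 and withdraw a patient whom the protocol properly admitted, or dose the patient and depart from 9.3.1. At stake are an avoidable burden on individual patients and inconsistent conduct. The validity of the efficacy estimate is not in question.

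**Working it through.** The protocol states no figure to reproduce. The check is a comparison of the rules along the patient's path, plus a sum of the burden borne before Day 0.

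**1. One permitted user, three urine tests**

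| Test | Source | Result for a permitted benzodiazepine user who is positive |
|---|---|---|
| Screening | 5.6.3; Table 1 referral row at the screening day; exclusion 15 | Exempt, so the patient proceeds |
| PET1, 1 to 7 days before dosing | 8.5.4; Table 1 at Day -3 | 8.5.4 states no consequence; exclusion 15 still exempts |
| Dosing morning | 9.3.1 | Dose cancelled, no rescheduling, patient withdrawn |

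The earlier tests may alert staff, but they do not stop the patient, because the exemption applies at both.

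**2. Does other text reconcile the rules?**

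- Section 7.2.2 relies on bedtime use. The exception also covers anxiety, which 7.2.2 does not discuss. Nor does it say that the urine will be negative.
- Section 17.9.1 makes allowance for pre-approved medication, but for review of abuse signals. It names Screening, Baseline and post-dose assessments, not the dosing morning.
- Exclusion 25 and the ongoing eligibility check in 8.5.1 allow staff to exclude such a patient earlier. Neither requires it.
- For opiates the two rules agree: "Prescription opiates must have been stopped at least 5x the elimination half-life of the specific drug at the time of inclusion", confirmed by a negative screen. Permitted benzodiazepines have no comparable condition.
- Section 9.3.1 gives discretion elsewhere. For raised blood pressure, Table 2 footnote 2 says: "Dosing may be rescheduled at the discretion of the site PI or study physician". The urine rule has no such clause.

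**3. Schedule check**

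The Table 1 columns after duration are web screen, screening day, MRI1, -10, -3, -2, -1, 0, 1, 2 to 7, 8 and 15. The urine row is filled in the fifth (Day -3) and twelfth (Day 15) columns; the eighth (Day 0) is blank. The Day 0 pregnancy test is missing in the same way, although 9.3.1 item 4 and section 22.3 require it.

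**4. Burden per affected patient between screening and Day 0**

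- Time (Table 1): MRI1 60 + lumbar puncture 60 + PET1 120 + preparation session 60 = 300 minutes.
- Radiation (section 12): 400 MBq × 0.006 mSv/MBq = 2.4 mSv.
- Samples: at least 5 ml CSF (8.5.3) and about 70 to 80 ml blood during PET1 (section 12 gives both figures).

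These are ordinary study procedures. The sum shows what one late withdrawal costs a patient; it says nothing about how often that would happen.

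**5. Effect on the analysis**

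Section 10.4.1 places randomization immediately before dosing. A patient stopped by the urine test is therefore most likely not yet randomized, and section 10.4 keeps such patients out of the Full Analysis Set. Even if randomization came first, the test precedes any study drug and treatment is blinded, so the result cannot depend on the arm.

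**The case against.** The strongest reply is that the conflict rests on an assumption. Section 9.3.1 speaks only of drugs of abuse and names no panel. If exclusion 15 supplies the panel, its exception could be held to come with it, leaving only a missing cross-reference. This is a fair limit on certainty. But 9.3.1 as written attaches withdrawal to a positive result without qualification, and site staff should not have to infer an exemption.

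A second reply is that eligibility and readiness to dose are separate gates. Section 7.2.6 asks patients to abstain from medicines that might interact with psilocybin or alter its effects, so a strict Day 0 rule could be deliberate. The permission to continue through the study is also worded for sleep medicines, which 7.2.2 expects to have cleared. This narrows the group at risk to anxiety users and to sleep users still positive in the morning. It does not explain why anxiety use is exempted at entry if it is to bar dosing.

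Third, staff learn of a positive result at screening and again before PET1, so the full burden in the working is a worst case. That stands, but nothing obliges them to act on it.

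Finally, the schedule omission is editorial: 9.3.1 lists the test as a numbered step and states its consequence. That also stands. The omission is worth correcting because section 8 treats the schedule as binding, but it is not evidence for the benzodiazepine conflict.

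**Conclusion.** The point holds as an inconsistency in conduct rules. On the assumption that the Day 0 panel is the one in exclusion 15, a patient admitted under the benzodiazepine exception and positive on dosing morning must be withdrawn for a permitted drug. If the Day 0 panel omits benzodiazepines, the conflict disappears, but the protocol does not say so. The gap in 5.6.3 and Table 1 exists either way.

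Three stronger inferences are not supported:

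- **That the trial result is threatened.** The loss occurs before dosing, under blind, and most likely before randomization; the effect on the primary comparison is minor.
- **That the number of patients can be estimated.** The documents give neither the frequency of benzodiazepine use nor a detection time. The number is unknown and probably small.
- **That benzodiazepine-positive candidates should be excluded at screening.** That would largely cancel the exception and work against the reason in 7.2.2 for keeping stable sleep users. A screening test 7 to 35 days before dosing also need not predict the Day 0 result.

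The correction is cheap and worth making.

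**What to change.** 1. In 9.3.1, state that a positive result explained by a documented benzodiazepine permitted under exclusion 15 does not by itself force cancellation or withdrawal, and that the Study Physician decides on dosing. Keep the rule strict for every other positive result.
2. Name the Day 0 panel in 9.3.1.
3. Add the Day 0 urine drug test and the Day 0 pregnancy test to 5.6.3 and Table 1.

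The cost is wording in 9.3.1 and 5.6.3 and a Table 1 entry. No procedure is added, since 9.3.1 already requires both tests. If the sponsor classes the change as substantial, section 24 requires approval before it is implemented. The downside is that a few patients may be dosed with residual benzodiazepine, at the physician's discretion.
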